#### Evaluating the effectiveness of SFL- data collection

Questionnaires are administered to participants by a research team member trained in data collection procedures to ensure standardised measurement and questionnaire administration. Questionnaires are administered one-to-one in the Sheds setting to account for potential literacy issues, prevent respondent burn-out, limit missing data and build rapport and trust between the researchers and Shedders. To also minimise missing data, participants will be contacted by the IMSA in the days before the research team visit the Sheds to perform data collection. Due to the informal nature of the Sheds, absence of data for a participant does will not necessarily indicate dropout from SFL. During 6 and 12 month follow-up in Phase 1, Cohort 2 were experiencing COVID-19 restrictions and therefore questionnaires were administered via phone in order to promote participant retention and complete follow-up. The questionnaire was designed via a consultation process with stakeholders involved in the design and delivery of SFL with a view to optimising acceptability for SFL participants and also SFL providers who were interested in evaluating their individual components of SFL. Participant demographics are recorded at baseline and include date of birth, living arrangements, educational attainment, employment status relationship and ethnicity. Participants are also asked how long they had been a Shed member and how often they attend the Shed. Core health and wellbeing outcomes measured at all-time points up to 12 months consist of; subjective wellbeing, help-seeking, physical activity, mental wellbeing, diet and cooking skills, social capital and self-efficacy. Participants are also asked how often they seek information about their health.

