#### Evaluating the effectiveness of SFL- data analysis

Questionnaire data is analysed using Statistical Packages for the Social Sciences (SPSS V 24). Descriptive statistics for each variable are calculated to inform participant characteristics. Intervention effect on health and wellbeing outcomes are determined by comparing the change scores from baseline to 3, 6 and 12 months, comparing data using inferential tests to identify significant differences set at *p* = 0.05. Analysis of subgroups based on criteria such as; Shed size location and timing of the intervention, will also be performed to identify significant differences in intervention effect between groups. Outcome data obtained from all participants are included in the data analysis, regardless of adherence to SFL. The intervention effects will be assessed at 3, 6 and 12 months based on those who completed follow-up at these time points. Assuming a worst case scenario for absentees i.e. that absentees failed to achieve a significant improvement in core health outcomes (physical activity, diet, mental wellbeing, subjective wellbeing, social capital and help-seeking), these worst- case scenario analyses will reflect the intention to treat principle. The numbers who achieved significant improvement at 3, 6 and 12 months will be presented as a percentage of those who were tested at these follow-up points. For the initial intervention effect worst-case scenario, the numbers who achieved significant improvements at 3 months will be presented as a percentage of those who were tested at baseline. The worst-case scenario for maintenance of this initial intervention effect will present the numbers who achieved significant improvements at 6 and 12 months as a percentage of those who were tested at the 3 month follow-up. Observed success rates will be compared between the intervention and comparison group in waiting using Chi-Square analysis.

A hybrid analytic approach of inductive and deductive analysis is applied to the participant transcripts. This means that whilst implementation frameworks are applied to inform implementation outcomes, the analysis process will remain open to findings that may emerge outside of those pre-set domains to allow assessment of intervention effect. In these circumstances, inter-rater reliability is used to cross-check coding strategies and interpretations are negotiated to agree on a ‘master’ code list.

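### The 6- and 12-month worst-case rates drop men not tested at 3 months, so they are conditional rates and not intention to treat

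*Protocol article*

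**What the plan says.** All the relevant rules are in the protocol article, under the heading on data analysis for the effectiveness of SFL.

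- **Observed rates.** At each visit the numbers improved "will be presented as a percentage of those who were tested at these follow-up points".
- **Worst-case rule and label.** The plan assumes that "absentees failed to achieve a significant improvement in core health outcomes", and states that "these worst- case scenario analyses will reflect the intention to treat principle". No worst-case rate is exempted from that label.
- **Worst case at 3 months.** Here "the numbers who achieved significant improvements at 3 months will be presented as a percentage of those who were tested at baseline".
- **Worst case at 6 and 12 months.** This is presented as a worst case for maintenance of the initial effect. It gives "the numbers who achieved significant improvements at 6 and 12 months as a percentage of those who were tested at the 3 month follow-up".

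The data-collection section adds that missing data for a man "will not necessarily indicate dropout from SFL". It also says that cohort 2 completed its 6- and 12-month questionnaires by phone under COVID-19 restrictions. The article gives no numbers tested at 3, 6 or 12 months.

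**The concern.** The rule and the later denominator conflict. Under the rule, an absent man is a failure. Under the 6- and 12-month denominator, a man absent at 3 months is not counted at all, even though he was tested at baseline. The earliest absentees, whom a worst-case analysis most needs to carry forward, are the ones removed.

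Two things are at stake. First, the main effects at 6 and 12 months rest on men who completed follow-up, and the worst-case rates are the stated check on attrition. A check that omits the earliest absentees is weaker than its label suggests. Second, the base changes between 3 months and the later visits, so a reader who sets the worst-case percentages side by side to judge sustained benefit is comparing rates in different groups of men.

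**Working it through.** The plan states no figure for these rates, so there is nothing to reproduce. The check is algebra, followed by labelled examples.

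**Notation.** n0, n3 and nt are the men tested at baseline, at 3 months and at a later visit t (6 or 12 months). x is the number improved at t.

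- Observed rate = x/nt
- Planned worst case = x/n3, if x counts every man improved at t
- Worst case on the baseline denominator = x/n0

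**Ratios that follow.**

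- Planned / baseline-denominator = n0/n3. This is above 1 whenever anyone is absent at 3 months.
- Planned / observed = nt/n3. This is above 1 only if more men are tested at t than at 3 months.
- Baseline-denominator / observed = nt/n0, which cannot exceed 1.

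**Size of n0/n3.** With a proportion a absent at 3 months it equals 1/(1 − a): 1/0.90 = 1.11 for 10% and 1/0.80 = 1.25 for 20%.

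**Examples.** I take n0 = 421, the Phase 1 participants in the sampling section, and assume that all were tested at baseline. Attendance and success rates are assumptions. Fractional counts are expected numbers.

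*A. Absence grows over time.* 10% absent at 3 months (n3 = 379), 20% absent at 12 months (n12 = 337), 50% of those tested improved at each visit.

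- 3-month worst case: 0.5 × 379 / 421 = 189.5/421 = 45.0%
- 12-month planned worst case: 0.5 × 337 / 379 = 168.5/379 = 44.5%
- 12-month on the baseline denominator: 168.5/421 = 40.0%

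The planned series reads 45.0% then 44.5%. On one base it reads 45.0% then 40.0%.

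*B. Same attendance at both visits.* 20% absent at 3 months and the same number tested at 12 months (n3 = n12 = 337), 50% improved at each.

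- 3-month worst case: 168.5/421 = 40.0%
- 12-month planned worst case: 168.5/337 = 50.0%
- 12-month on the baseline denominator: 168.5/421 = 40.0%

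Nothing has changed between visits, yet the planned series rises by 10 points because the base changed.

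*C. Effect of the numerator reading.* n3 = 337; 95% of these are seen at 6 months (320); half of the 84 men absent at 3 months return (42), so n6 = 362; 40% of those tested improved.

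| Rate at 6 months | Calculation | Result |
|---|---|---|
| Observed | 144.8/362 | 40.0% |
| Planned, all improved men in the numerator | 144.8/337 | 43.0% |
| Planned, numerator limited to men tested at 3 months | 128/337 | 38.0% |
| Baseline denominator | 144.8/421 | 34.4% |

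In this example both readings of the plan lie above the baseline-denominator rate. Only the first lies above the observed rate.

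**The case against.** **The rate is named as a maintenance measure.** The plan separates the initial effect, with a baseline denominator, from maintenance of that effect, with a 3-month denominator. The change of base is disclosed, and a rate among men seen after the programme is a legitimate descriptive quantity. This stands as a reason to allow a conditional rate. It does not rescue the intention-to-treat label, which the plan applies to the worst-case analyses without exception.

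**The numerator may already be matched.** A reader might infer that men who missed 3 months and came back are counted in the numerator while absent from the denominator, so that the worst case comes out above the observed rate. The documents do not establish this. The numerator is given only as "the numbers who achieved significant improvements at 6 and 12 months". No restriction is stated, but a percentage of a group is ordinarily read as counting members of that group. The sentence that includes outcome data from all participants concerns adherence. The data-collection section leaves return after a missed visit possible, but does not say that it is expected. Even on the unrestricted reading, the excess needs more men tested at 6 or 12 months than at 3 months, and it cannot arise if men who leave never return. No counts show which situation applies.

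**The 20% is not a 3-month loss.** The sampling section gives 20% as a dropout allowance with no time point. Its use at 3 months above is illustrative only.

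**The consequence is limited.** The stated chi-square comparison uses observed success rates, and intervention effects rest on change scores. No stated test uses the 6- and 12-month worst case, and the observed rates are reported as well. This stands, and it lowers the weight of the point.

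**Conclusion.** The point holds as an inconsistency between denominator and label. The 6- and 12-month worst-case rates exclude baseline men absent at 3 months, so the statement that these analyses "will reflect the intention to treat principle" does not fit them. They also cannot be compared directly with the 3-month worst case. This conclusion follows from the stated denominators and does not depend on how the numerator is read.

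The size does depend on assumptions. With all improved men in the numerator, the inflation over a baseline denominator is n0/n3, or 1.11 to 1.25 for an assumed 10% to 20% absent at 3 months. With a restricted numerator the gap depends on how many absentees return and how they fare. It was 38.0% against 34.4% in example C. That the worst case would exceed the observed rate is a conditional possibility only and should not be reported as a property of the plan.

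The correction should be made before the 6- and 12-month rates are reported. Because the rates are supplementary and descriptive, the error does not undermine the stated group comparison.

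**What to change.** Use all men tested at baseline as the worst-case denominator at 3, 6 and 12 months, and count men absent at the visit in question as not improved. That rate agrees with the plan's own rule, cannot exceed the observed rate, and can be compared across visits.

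If a maintenance rate is also wanted, draw both numerator and denominator from the men tested at 3 months, state that it is conditional on 3-month testing, and do not describe it as intention to treat.

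The change costs about one sentence in the data-analysis section and a recount of data already collected. The reported 6- and 12-month worst-case percentages will generally be less favourable.

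### The one test that names the wait-list compares 'observed' success rates, so on the natural reading the controlled result is completer-only, and the rates labelled intention to treat are never compared between arms

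*Protocol article*

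**What the plan says.** All the relevant text is in one paragraph of the Protocol article, Part 1, under the heading on data analysis for effectiveness.

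- **Analysis set.** "The intervention effects will be assessed at 3, 6 and 12 months based on those who completed follow-up at these time points".
- **Ordinary success rate.** The number improved at each time point "will be presented as a percentage of those who were tested at these follow-up points".
- **Worst-case rate.** Absentees are assumed not to have improved, and "these worst- case scenario analyses will reflect the intention to treat principle". At 3 months, "the numbers who achieved significant improvements at 3 months will be presented as a percentage of those who were tested at baseline". For maintenance, the numbers are given "at 6 and 12 months as a percentage of those who were tested at the 3 month follow-up".
- **Test against the wait-list.** "Observed success rates will be compared between the intervention and comparison group in waiting using Chi-Square analysis".
- **Change scores.** Effects are also "determined by comparing the change scores from baseline to 3, 6 and 12 months", with inferential tests to "identify significant differences set at *p* = 0.05". No comparator is stated for these tests.

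The section on participants and sampling gives 212 men in 12 clusters for the first cohort and 89 men in 3 clusters for the wait-list comparator, with a general allowance of 20% for dropout. The data-collection section warns that a man with no data has not necessarily left the programme.

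**The concern.** The plan takes the trouble to define a rate that keeps absentees in the denominator and links it to intention to treat. It attaches no test and no wait-list comparison to that rate. The comparison with the wait-list is written for the *observed* rates, which, set against *worst-case*, most naturally means the rates among men tested.

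The controlled comparison then rests on whoever was present at follow-up. One arm is going through a 10-week programme and the other is waiting for it, so equal absence cannot be taken for granted. If absence differs by arm and is related to improvement, the difference among men tested is biased. The bias could favour either arm: disengaged men could be missing from the SFL side, or men with nothing yet to attend for could be missing from the wait-list side. As planned, a reader would see worst-case percentages without a matching comparison and could not tell whether the controlled conclusion depends on who was absent.

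**Working it through.** **1. Which rate goes where.**

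| Quantity | Denominator | Test against wait-list stated? |
|---|---|---|
| Ordinary success rate | Men tested at that follow-up | Yes, if this is what *observed* means |
| Worst case, 3 months | Men tested at baseline | No, percentage only |
| Worst case, 6 and 12 months | Men tested at 3 months | No, percentage only |
| Change scores | Men who completed follow-up | Comparator not stated |

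If the change-score tests are between-group, they too use only men who completed follow-up. No row attaches a wait-list test to a rate that counts absentees. The 6- and 12-month worst-case rates also lose men absent at 3 months, so they are not calculated over all baseline men.

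**2. Inputs for the size.** From the article: 212 SFL men and 89 wait-list men. There is no planned figure to reproduce, because the article states no success rate and no absence by arm. Both are assumed below and varied. The 20% dropout figure in the sampling section is an overall allowance, not an arm-specific rate.

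**3. Formulae.** With *s* men improved, *N* men at baseline and absence *a*: men tested *n* = *N*(1 − *a*), rounded; observed rate = *s*/*n*; baseline-denominator rate = *s*/*N*. Each pair is compared by Pearson chi-square without continuity correction, ignoring clustering.

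**4. Assumed success among men tested of 40% SFL v 25% wait-list.**

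| Absence SFL / wait-list | Observed | p | Baseline denominators | p |
|---|---|---|---|---|
| 20% / 20% | 68/170 = 40.0% v 18/71 = 25.4% | 0.030 | 68/212 = 32.1% v 18/89 = 20.2% | 0.038 |
| 20% / 10% | 68/170 = 40.0% v 20/80 = 25.0% | 0.021 | 68/212 = 32.1% v 20/89 = 22.5% | 0.095 |
| 30% / 10% | 59/148 = 39.9% v 20/80 = 25.0% | 0.024 | 59/212 = 27.8% v 20/89 = 22.5% | 0.335 |
| 10% / 20% | 76/191 = 39.8% v 18/71 = 25.4% | 0.030 | 76/212 = 35.8% v 18/89 = 20.2% | 0.008 |

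With equal absence the two analyses agree. With unequal absence they separate, and the last row shows the baseline-denominator result moving in favour of SFL.

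**5. No true difference, every absentee unimproved.** This assumption is the least favourable to the observed comparison.

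- Moderate split: 64/212 = 30.2% and 27/89 = 30.3% improved. With 42 SFL men (20%) and 4 wait-list men (5%) absent, observed rates are 64/170 = 37.6% v 27/85 = 31.8%, a spurious 5.9 points, p = 0.36.
- Wide split: 53/212 = 25.0% and 22/89 = 24.7% improved. With absence of 40% v 10%, observed rates are 53/127 = 41.7% v 22/80 = 27.5%, p = 0.038.

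**6. No true difference, absence unrelated to improvement.** With 30% success in both arms and absence of 20% v 5%, observed rates stay at about 30% each. Baseline denominators give 0.30 × 0.80 = 24.0% v 0.30 × 0.95 = 28.5%, a spurious deficit of 4.5 points for SFL.

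**The case against.** **The plan makes no intention-to-treat claim for the chi-square test.** This stands. A reader might infer that the plan contradicts itself by promising intention to treat and then testing completers. The text does not support that: the label is attached to the worst-case analyses only, and the use of men who completed follow-up is stated openly. What remains is a gap between the two, because the rate with the intention-to-treat label is never compared with the wait-list.

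**The word *observed* is undefined, and a condensed article may leave denominators to a fuller document.** This stands in part. The completer reading is the natural one, not an explicit statement. But the article itself chooses the test, the rate to be tested and the absentee rule, so asking that they be joined up is fair.

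**It may not be the only controlled test.** This stands as to wording. The change-score tests could be between-group, and Table 2 describes a controlled trial. The accurate statement is that the chi-square is the only test that names the wait-list.

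**Absence is not the same as disengagement.** This stands. The data-collection section says so, and describes contact before visits and one-to-one administration in the Shed to limit missing data. A reader might infer that the observed comparison must inflate the SFL benefit. The documents give no absence by arm and do not support a direction.

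**Counting absentees as failures is not neutral.** This also stands. Step 6 shows it producing a spurious harm, and the last row of step 4 shows it enlarging a benefit. It is therefore no automatic replacement for the completer comparison.

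**Conclusion.** The point holds as a gap in the specified comparison. On the natural reading of *observed*, the only test naming the wait-list is completer-only, and the worst-case rates said to reflect intention to treat are presented without any comparison between arms. The controlled result is exposed to bias if absence differs by arm, in an unknown direction.

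The size cannot be fixed from the article. In the illustrations it runs from almost nothing under equal absence (p = 0.030 v 0.038) to a changed conclusion under absence of 20% v 10% (0.021 v 0.095) or 30% v 10% (0.024 v 0.335). A false positive where there is no true difference needed a wide split and every absentee unimproved (40% v 10%, p = 0.038); the 20% v 5% split gave 5.9 points and p = 0.36. All of these rest on assumed success and absence rates, with only the arm sizes taken from the article, and none allows for clustering.

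The documents do not support saying that the SFL effect will be overstated, or that the baseline-denominator analysis should take over as the main one.

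**What to change.** 1. State the denominator of the *observed* success rates used in the chi-square comparison.
2. Also run the 3-month SFL v wait-list comparison on all men tested at baseline in each arm, applying the plan's own absentee rule identically to both.
3. Present this beside the completer comparison, and report the 3-month absence rate by arm with them.
4. Say in advance that neither result is to be read alone, and that a conclusion which changes between the two will be reported as sensitive to absence.

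The cost is a sentence or two and one extra table from data already held. The downside is that the added analysis can shrink or enlarge the difference, so the authors may have to report a less clear-cut conclusion.

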#### Participants and sampling

Respecting the autonomous and informal environment of the Sheds is an important factor in delivering health promotion through Sheds [27, 33]. Therefore, Sheds are recruited to participate in the SFL programme and evaluation via purposive sampling using an expression of interest process with the objective to deliver SFL in a diverse range of Shed settings (small/large, urban/rural). All adult males in the Sheds setting were eligible to participate in the study providing they had good proficiency of the English language and could give informed consent. A sample size estimation was undertaken using G*Power 3.1.9.2 software using physical activity (PA) as the key outcome measure, whereby it was calculated that 106 participants would be required for a trial in which participants were individually randomised (the decision to use PA as the primary outcome measure was determined through consultation with Shedders who requested that PA be a key focus of SFL during the initial pilot phase). However a clustered design in which SFL was delivered to small clusters of men within Sheds was more preferable to honour the Shed ethos whilst also ensuring a wide geographical spread. For this reason a design with circa 20 men in each cluster was estimated. A previous study with middle-aged men suggested that this design effect is ~ 2.4, thus increasing the sample size required to 255 [47]. Allowing for a 20% dropout based on a sample size estimation, the final total required was 306 or 15 clusters. In the event of low participation within clusters, it was decided that SFL would be targeted at clusters with similar representation. In Phase 1, 421 Shedders participated across 22 clusters and these were divided into two cohorts. Whilst delivery occurred in the first cohort (*n* = 12 clusters; *n* = 212 Shedders) a wait list control cohort served as a comparator (*n* = 3 clusters; *n* = 89 Shedders) and these were a subset of the second cohort (*n* = 9 clusters, *n* = 209 Shedders). Fourteen clusters were in urban areas and 8 were in rural areas across counties; Kildare (in Ireland’s mid-east region with a population of ca. 222, 504), Waterford (in Ireland’s south-east region with a population of ca. 116,176), Limerick (in Ireland’s south-east region with a population of ca. 194,899) and Louth (in Ireland’s mid-east region with a population of 128, 884) [48]. Participants were recruited for Phase 1 across Waterford and Kildare in March to May 2019 and Limerick and Louth in September to December 2019. Participants for Phase 2 will be recruited from September to December 2021 (recruitment was postponed until this date due to COVID-19 restrictions).

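### The sample size allows for clustering by Shed (design effect about 2.4), but the one between-group test the article names is a chi-square on individual men, which does not

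*Protocol article*

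**What the plan says.** The Participants and sampling section starts from an individually randomised calculation keyed to physical activity: "106 participants would be required for a trial in which participants were individually randomised". It sets that aside because delivery is to groups of men within Sheds, for which "a design with circa 20 men in each cluster was estimated". It continues: "A previous study with middle-aged men suggested that this design effect is ~ 2.4, thus increasing the sample size required to 255". After an allowance for dropout it arrives at 306 men or 15 clusters. The same section gives the controlled layout: 12 clusters and 212 men receiving the programme in the first cohort, against a wait-list comparator of 3 clusters and 89 men.

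The section on data analysis for effectiveness handles change scores by "comparing data using inferential tests to identify significant differences set at *p* = 0.05", without naming the tests. It then defines success rates as the number of men with significant improvement, as a percentage of men tested at follow-up or, in the worst-case version, at an earlier time point. On these it states: "Observed success rates will be compared between the intervention and comparison group in waiting using Chi-Square analysis". Nowhere does the article mention a mixed model, GEE, cluster-robust errors, a Shed-level summary or an adjusted chi-square.

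**The concern.** The two sections rest on incompatible assumptions. The sample size accepts that men in the same Shed resemble one another and puts a figure on it. The chi-square counts each man as a separate, independent observation. Enlarging the sample for clustering protects power only if the analysis then uses the larger variance. It does nothing for the error rate of an unadjusted test.

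At stake is the named comparison of success rates between intervention and wait-list. With three comparator Sheds, ordinary Shed-to-Shed variation could produce a significant difference more often than the stated 5%. The Discussion says the findings will help decide effectiveness and scale-up, and the Dissemination section plans a final report aimed at policy makers and service providers.

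**Working it through.** **Inputs, all from the protocol article.** Individually randomised size 106; about 20 men per cluster; design effect (DE) about 2.4; significance level 0.05; intervention 12 clusters, 212 men; wait-list 3 clusters, 89 men; dropout 20%.

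**The plan's own figures.** 106 × 2.4 = 254.4, rounded up to 255, so the stated 255 reproduces. 255 × 1.2 = 306, so the final total also reproduces in that form.

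**Implied ICC.** DE = 1 + (m − 1) × ICC. With m = 20, ICC = (2.4 − 1)/(20 − 1) = 0.074. This assumes that the 2.4 refers to clusters of 20.

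**Error of the unadjusted test at the planning value.** The test statistic's variance is inflated by DE, so the actual two-sided error is 2 × [1 − Φ(1.96/√DE)]. With DE = 2.4, √2.4 = 1.55 and the error is **20.6%**. Intervals would need to be about 1.55 times wider.

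**Error at the actual layout, no loss.**
- Intervention: 212/12 = 17.7 men per cluster, DE₁ = 1 + 16.7 × 0.0737 = 2.23.
- Wait-list: 89/3 = 29.7 men per cluster, DE₂ = 1 + 28.7 × 0.0737 = 3.11.
- Pooled DE = (DE₁/212 + DE₂/89)/(1/212 + 1/89) = 2.85.
- Error = 2 × [1 − Φ(1.96/√2.85)] = **24.6%**.

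**Same layout with 20% lost evenly.** Pooled DE = 2.47, error **21.2%**.

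**Simulation check.** A beta-binomial simulation (200,000 runs; 12 against 3 clusters; 212 against 89 men; ICC 0.074) of the uncorrected Pearson chi-square gave 25.0% to 25.4% for true success rates of 20%, 30% and 50%. With the ICC set to practically zero it gave about 5%, so the clustering causes the excess. With a Yates correction it gave about 21% to 22% with no loss; a further simulation with 20% loss gave about 18%.

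**Sensitivity to the ICC (actual layout, no loss, no continuity correction).**

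| ICC | Pooled DE | Actual error at nominal 5% |
|---|---|---|
| 0.01 | 1.25 | 8.0% |
| 0.02 | 1.50 | 11.0% |
| 0.05 | 2.26 | 19.2% |
| 0.074 (implied by the protocol) | 2.85 | 24.6% |
| 0.10 | 3.51 | 29.6% |

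**Cluster count.** The article gives 22 clusters in Phase 1, but its cohorts are 12 and 9, which sum to 21. If the first cohort had 13 clusters, the error at ICC 0.074 would be 24.3%, so the discrepancy hardly matters to this result.

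**The case against.** Four points deserve weight.

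*A separate analysis plan may adjust for clustering.* It may, and silence in an article would not be a fault. But on this comparison the article is not silent. It names a chi-square on percentages of men, and that choice conflicts with its own sample-size basis.

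*The change-score tests may be sound.* This stands. A reader might infer that the whole effectiveness analysis ignores Sheds. The documents do not support that: they mention "comparing the change scores from baseline to 3, 6 and 12 months, comparing data using inferential tests" and do not say how Shed is handled, and the choice of model is commonly left to an analysis plan.

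*The chi-square is not the only controlled comparison.* This also stands. A reader might move from the only named between-group test to the only controlled evidence. But the intervention effect is said to be determined from change scores, Table 2 calls the design a pragmatic controlled trial, and the unnamed tests may also compare the groups. The chi-square is not designated as primary.

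*The size of the inflation is conditional.* The 2.4 is borrowed from a previous study and used in a calculation for physical activity. The success rates are dichotomised improvements across several core outcomes, and the article gives no ICC for any of them. It would be too strong to say flatly that the error rate is 21% to 25%. What stands without that condition is that any positive within-Shed correlation pushes the unadjusted chi-square's error up in this layout.

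**Conclusion.** Wrong as written, for the chi-square sentence. The test assumes independence between men whom the protocol itself plans as correlated within Sheds. If the planning design effect carries over to the success outcomes, the nominal 5% error is about 21% at a design effect of 2.4, about 25% at the actual layout, and about 21% at that layout with 20% even loss. These figures assume no continuity correction and a design effect referring to about 20 men per cluster. A lower ICC or a continuity correction reduces the excess; at an ICC of 0.01 the uncorrected test's error is still about 8%. No finding is made against the unnamed change-score tests.

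**What to change.** Replace the chi-square with a comparison that respects Sheds. The preferred choice is a t-test on Shed-level success proportions, intervention against wait-list, with 12 + 3 − 2 = 13 degrees of freedom. Treat 13 as provisional until the cluster counts (12 + 9 against 22) are reconciled. A mixed model with a random Shed effect and small-sample degrees of freedom is an alternative. With only 3 comparator Sheds, a logistic GEE or GLMM is fragile even with a correction and should not be the main analysis of success rates.

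Add a sentence that the change-score tests also account for Shed, and report the observed ICC for each outcome so that the 2.4 can be judged.

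The change is to analysis wording only. It needs no new data, provided that Shed membership is kept in the analysis file. The price is wider intervals and less favourable p-values. It corrects the error rate for clustering only: the cohorts were recruited in different counties and at different times of year without randomisation, and confounding by county or season remains.
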